#### Shared Decision Making and the offer of lung cancer screening

Participants who meet risk threshold or criteria based eligibility for LCS will be offered a Shared Decision Making process. This process will provide them with a decision aid, which will contain information about screening in general, and lung cancer screening in particular (including risks and benefits, possible findings, follow up of CT scan findings etc.) allowing them to make an informed decision about whether to proceed with screening. Whānau are welcome and invited to participate at all stages of the Shared Decision Making process. If they choose to proceed, written consent will be obtained and an appointment will be made for them to undergo the scan. The shared decision making process can be undertaken in-person, by phone or using a digital platform (secure telehealth platform) immediately following the risk assessment or at a later date, according to the person’s preference. Where people opt for a phone or digital platform based decision making process we will be able to provide them with the same information and resources used in an in-person process. The study team has developed a shared decision making guide, and adapted a decision aid supported by health literacy experts, which is included in Appendix 4.

#### Offer to participate in COPD assessment

Participants who are eligible for LCS (by LDCT) will also receive written information about COPD assessment. After they have undergone Shared Decision Making for LCS, the study nurse will explain the COPD assessment and offer them the opportunity to participate. They will be asked for their written consent to proceed with COPD assessment.

### CT scan

Scans will be undertaken at certified private community radiology providers who will operate equipment which meets the minimum specification for dose and slice thickness parameters for low dose lung screening CT examinations.

The radiology provider will provide a summary report on the imaging stating that the scan was conducted for research, and the scan will then be sent to the research radiologist where it will be reviewed by them or their registrar within a few days of the scan being conducted.

The images will be pulled as thin section CT data to ADHB and WDHB where the images will be reviewed by dedicated named radiologists who will complete a standardised proforma report of findings of interest to the study including: lung nodules, structural lung disease e.g. emphysema and interstitial lung disease, significant airways disease e.g. bronchiectasis, and other incidental findings. Where nodules are present, lung nodule volumetry will be performed and recorded in the report. The report will be sent to the participant’s GP, the study respiratory physician and the study co-ordinator. CT scan result management and follow up is detailed below.

### COPD assessment

The COPD assessment nurses will meet the participants at the radiology centre when they attend for their CT scan and the COPD assessment will be undertaken after the CT scan. This will include assessment of the participant’s COPD-related symptoms (using the COPD Assessment Test) and spirometry to determine the presence and extent of airflow limitation. A CAT score $>$ 10 will be used as the threshold for regular treatment. Spirometry will be performed using a portable spirometer (Easy-One^TM^; ndd Medizintechnik AG, Zurich, Switzerland) using the standardised process recommended by the New Zealand Medical Association^63^ with the highest value of the best three acceptable blows used for classification of COPD status. A forced expiratory volume (FEV1) to forced vital capacity (FVC) ratio of less than 70% of the expected result for that participant’s age and sex (FEV1/FVC < 0.70) is diagnostic of airflow limitation (COPD)^1,36^. These FEV1 results are then categorised according to NZ guidelines Following the first test, the spirometry will be repeated using a bronchodilator in order to assess COPD severity.

This will be undertaken using a standardised protocol by Māori nurses trained in undertaking spirometry and the study procedures.

Data will be collected from the participant (spirometry, symptom assessment, patient-reported diagnosis, medications and health service utilisation), GP and hospital records (COPD and related classifications, COPD management and health service utilisation in the 12 months prior to assessment), and the LCS trial (demographics, quality of life, smoking, comorbidities).

Participants will also be asked to complete a post-COPD assessment evaluation questionnaire (Appendix 16)

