In Aotearoa NZ, COPD is under-diagnosed, particularly early in the disease course, but the degree of current unmet need among the high-risk Māori population is unknown. While some information about the prevalence of severe COPD can be gathered from those who are hospitalised for the disease, little is known about the true burden of COPD in the community among those with milder forms of the illness. In primary care, COPD is under-diagnosed and therefore under-treated.^1,2,30-34^ This is due to a combination of factors, including the non-specific symptoms,^2,3,27^ slow onset of disease and lack of systematic consideration.^35^ There is a dearth of evidence about the extent to which COPD is under-diagnosed in primary care.

There are some clear criteria for how to diagnose and assess COPD severity. A diagnosis of COPD should be considered in patients with symptoms suggesting COPD (dyspnea, cough, sputum, wheeze, recurrent lower respiratory tract infections) and/or a history of exposure to risk factors for the disease, and confirmed by spirometry results consistent with persistent airflow limitation^1,36^. The severity of airflow limitation can be categorised into mild, moderate, severe and very severe. Although spirometry is used to diagnose and assess the severity of airflow obstruction, further assessment of symptoms is needed. The COPD Assessment Test (CAT) is an 8 item, validated tool that quantifies symptom burden and impact on wellbeing and daily life. It is recommended for, and widely used, in routine practice^1,37^. Electronic and paper versions are available^37,38^. CAT scores range from 0 to 40.

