#### Secondary outcomes:

In addition, the trial will include the assessment of outcomes needed for the development of a national screening programme, including:

Participants and whānau experience of LCS:

- What is the participant and provider experience of LCS?
- What is the experience and acceptability of the shared decision making and results management processes as outlined in the protocol?
- What is the participant burden using the tools outlined in the study methods?
- What is the provider burden using the processes outlined in the GP clinic based arm of the study?

Parameters relating to recruitment and participation in the LCS pathway:

- What is the accuracy of recording of smoking history in general practice among those who are identified as potentially eligible for risk assessment i.e. those who are not recorded as ‘never smokers’?
- What % of Māori aged 55-74 in a general practice are potentially eligible for lung cancer screening
- What % of potentially eligible people agree to undergo risk assessment
- What % of those undergoing risk assessment are eligible for lung cancer screening
- What % of those eligible for lung cancer screening decide to proceed with screening
- What % of those who decide to proceed with screening attend their appointment for screening
- We have also included in our risk assessment a question about work place related exposure risks for lung cancer. The data from this question will contribute to a wider NZ study of lung cancer related to work place exposure.
- In addition, we will also ask participants about their lifetime exposure to passive smoking, using questions taken from the Lung Health Questionnaire developed for the International Lung Screening Trial (ILST). This data is collected using a standard validated scale, used in ILST and European trials, and will contribute to a future planned study of the relevance of the PLCO_M2012_ to the NZ population and how we can develop a more accurate risk model, particularly for Māori.

Parameters relating to the assessment of COPD within LCS:

- What is the prevalence of COPD among participants who proceed to CT scanning
- What are the characteristics of COPD in those assessed and diagnosed
- How are participants with COPD managed within primary care following this assessment
- How do GPs change the way they manage COPD after they are provided with COPD results and management recommendations
- What is the participant experience of COPD assessment

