### Secondary outcomes

Secondary outcomes include:

**Eligibility for risk assessment:** Proportion identified as potentially eligible by PHO list who were eligible for risk assessment.

**Completion of Risk assessment:** Proportion of participants who were eligible for risk assessment that completed the risk assessment process. Also an assessment of the differences between the primary care and central hub groups.

**CT scan eligibility:** Proportion of those who underwent risk assessment that met risk threshold for a CT scan by PLCO_M2012_ and criteria-based eligibility.

**Effectiveness of engagement in shared decision making:** proportion of eligible participants that decide to proceed with screening after participating in a shared decision making process to discuss the risks and benefits.

**LCS screening uptake among those eligible:** proportion of those that agree to lung cancer screening who attended and underwent the scan.

- Participant and provider experience of LCS
- Experience and acceptability of the shared decision making and results management processes
- Participant burden using the tools outlined in the study methods
- Provider burden using the processes outlined in the GP clinic based arm of the study
  - The burden on staff and participants will be measured through follow-up interviews and/or focus groups conducted by a member of the research team following the implementation of the pilot.
- Provision of a description of LCS outcomes. This will include The positivity rate of CT scans; the proportion of scans with incidental findings; proportions who proceed to nodule management (interval scans); diagnostic investigations; incidental finding management; the number, stage and types of cancers; response to brief advice to quit; and smoking cessation medications provided and referrals made.
- Assessment of the accuracy of recording of smoking history in general practice

**Prevalence of COPD among those eligible for LCS:** proportion of those eligible who have a spirometry-based COPD diagnosis.

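### The COPD criterion is written in two non-equivalent ways, and COPD prevalence has conflicting denominators: the same 200 expected cases give 17.6%, 40.0% or 50.0%

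*Protocol*

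**What the plan says.** **Criterion.** In the COPD assessment section under study procedures, one sentence gives the diagnostic rule twice, calling an FEV1/FVC ratio "less than 70% of the expected result for that participant’s age and sex (FEV1/FVC < 0.70) is diagnostic of airflow limitation (COPD"). The prose sets the cut-off relative to an expected value; the bracket sets it as a fixed number.

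**Which test.** The same paragraph goes on: "Following the first test, the spirometry will be repeated using a bronchodilator in order to assess COPD severity". Severity is the only purpose given for the second test, and no sentence says which test classifies COPD status. The Background section on COPD says a diagnosis should be "confirmed by spirometry results consistent with persistent airflow limitation".

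**Who is tested.** Spirometry takes place at the radiology centre, where "the COPD assessment will be undertaken after the CT scan". The exclusion criteria remove people who decline or cannot do spirometry from this part of the study.

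**Denominator.** Three are in use:

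- Outcomes and Significance, Secondary outcomes, under a heading that refers to people eligible for lung cancer screening: "proportion of those eligible who have a spirometry-based COPD diagnosis".
- Full trial, Secondary outcomes: "What is the prevalence of COPD among participants who proceed to CT scanning". The Synopsis objectives likewise refer to people who have the LDCT.
- Sample size text for the COPD assessment: the 50% that yields 200 cases is taken of the 400 people assessed.

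**The concern.** The two wordings of the criterion agree only if the expected FEV1/FVC ratio is 1. FEV1 is part of FVC, so an expected ratio is below 1 and the percent-of-expected wording is always the stricter of the two. A participant whose ratio lies between the two cut-offs has COPD under one half of the sentence and not under the other.

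COPD status determines the numerator of the prevalence result, who enters the analysis of change in GP management, and whether the 200 cases behind the stated 85% power will be found.

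The denominator is a separate problem. If prevalence is taken over everyone eligible for screening, most of the denominator never had the test that defines the numerator. The result then mixes COPD prevalence with uptake of scanning and of spirometry. It would not be comparable with the 37-57% that the Background cites from programmes where spirometry was done in about 98-99% of people.

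**Working it through.** **Inputs, all from the Protocol**

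| Quantity | Value | Where |
|---|---|---|
| Expected eligible for LDCT | 1134 | Synopsis, expected sample size |
| Expected scanned | 500-550 | Synopsis, expected sample size |
| Expected COPD assessments | 400 (80%) | Sample size text, COPD assessment |
| Expected COPD cases | 200 (50%) | Sample size text, COPD assessment |
| Management test | n = 200, 10% vs 17%, 5% level, 85% power | Sample size text, COPD assessment |

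**1. Reproduce the plan's figures.** 500 × 0.80 = 400, and 400 × 0.50 = 200. So the 80% is taken of 500 scans and the 50% of those assessed.

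Power of the one-sample proportion test (normal approximation, two-sided 5%):

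Φ{[(p1 − p0)√n − 1.96√(p0(1 − p0))] / √(p1(1 − p1))} = Φ{[0.07 × 14.142 − 1.96 × 0.300] / 0.3756} = Φ(1.07) = 85.8%.

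The stated 85% therefore reproduces at n = 200. The sidedness is not stated; the one-sided version gives 90.7%.

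**2. Denominator.** The same 200 cases over each stated denominator:

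| Denominator | Prevalence | People in it without spirometry |
|---|---|---|
| 400 assessed | 200/400 = 50.0% | 0 |
| 500 scanned | 200/500 = 40.0% | 100 (20%) |
| 550 scanned, still 200 cases from 400 assessed | 200/550 = 36.4% | 150 (27%) |
| 1134 eligible | 200/1134 = 17.6% | 734 (65%) |

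Relative to those tested, the eligible-based figure is lower by a factor of 50.0/17.6 = 2.8, which is 1134/400. The scan-based figure at 500 scans is lower by 50.0/40.0 = 1.25. This step needs no outside assumption.

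**3. Criterion.** Write E for the expected ratio. The prose means FEV1/FVC < 0.70 × E; the bracket means FEV1/FVC < 0.70. The Protocol gives no E. Assuming E between 0.75 and 0.80:

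- 0.70 × 0.75 = 0.525
- 0.70 × 0.80 = 0.56

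The prose would then be an absolute cut-off of 0.525-0.56, against 0.70 in the bracket. The number of people between the two depends on the distribution of the ratio in this population, which the documents do not give.

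**4. Sensitivity of the power to the case count.** The formula in step 1 gives 61.7% at 100 cases and 40.2% at 50 cases. These counts are illustrations, not forecasts. They show only that the 85% depends on the 200 cases, and so on which criterion is applied.

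**5. Classifying test.** The procedures section states the diagnostic rule, then introduces the repeat test for severity. The Background asks for limitation that persists. The two can be reconciled, but the text does not do it, and two staff members could classify the same participant from different tests. No size can be put on this.

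**The case against.** The bracketed 0.70 is the only explicit numeric cut-off for the ratio, and the surrounding prose can be read as a garbled gloss on it. The GP letter section supports this: it attaches a percent of predicted to FVC and FEV1 and lists the ratio without one. The planned 50% would also be hard to sustain under the prose, which suggests the planners did not use it. These points bear on what was probably meant. They do not remove the contradiction from the sentence that staff will follow.

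A reader might infer that the criterion conflict makes prevalence wrong several-fold. The documents do not support that. It requires ignoring the printed 0.70, and it rests on an assumed expected ratio plus an assumed spread.

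A reader might also infer that diagnosis is fixed on the pre-bronchodilator test. That follows only from sentence order; the text is ambiguous, and the reference to persistence is background.

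On the denominator, a reader might infer that the plan counts untested people as free of COPD. No passage says so. It is only the arithmetic consequence of one definition read literally. The protocol uses the word eligible loosely elsewhere, and eligible for COPD assessment may have been meant, although the outcome's own heading refers to lung cancer screening. Under the scan-based definitions the dilution is 1.25-fold at 500 scans, not 2.8-fold. Nor does the denominator touch the 200 cases, the 85% power or entry to the management analysis; those depend on the case count alone.

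An analysis plan would commonly fix denominators. Here, though, the protocol itself states conflicting ones. Measured FEV1 and FVC are to be reported, so much can be reclassified at analysis. That lowers the severity, but it does not alter the result already given to the participant and the GP.

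**Conclusion.** Wrong as written, of moderate severity. One sentence gives two non-equivalent criteria for COPD, the classifying test is not clearly named, and the stated prevalence denominators conflict.

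The denominator effect follows from the protocol's own counts: 17.6%, 40.0% (36.4% at 550 scans) or 50.0% from the same 200 cases. The definition under Outcomes and Significance, read literally, understates prevalence among those tested 2.8-fold.

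The size of the criterion effect cannot be determined from the documents. With an assumed expected ratio of 0.75-0.80, the prose means a cut-off of 0.525-0.56. That would put the assumed 200 cases, and with them the 85% power, in doubt. Under the bracketed wording the plan's figures stand.

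COPD is a nested secondary sub-study, and the comparison of invitation strategies is unaffected.

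**What to change.** - **Criterion and test.** In the COPD assessment procedures, reconcile the two wordings into one criterion and state which test, first or bronchodilator, classifies COPD for the endpoint, consistently with the Background. The choice is clinical and is not made here.
- **Sensitivity analysis.** Report prevalence under the alternative criterion and the alternative test, keeping FEV1 and FVC from both tests for this purpose.
- **Denominator.** Amend the prevalence outcome under Outcomes and Significance, and align the Synopsis objective and the Full trial question, so that prevalence = COPD cases / participants with acceptable spirometry. Show the eligible, scanned and assessed counts beside it, so that selection into testing is visible.

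The cost is protocol wording and table definitions. Both spirometry tests are already performed, so no visit, procedure or sample size changes.

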### Nodule assessment, classification and management

A variety of nodules, with different levels of risk of actually being cancer, are expected to be identified by the lung CT scan. All identified nodules will require follow up and further consideration. Diagnostic assessment, such as bronchoscopy or biopsy, used in the investigation of nodules have potential harms for the patient. These harms can be minimised by minimising the number of diagnostic procedures performed on nodules that are not cancer. This can be achieved through the use of cancer risk thresholds and repeat short interval scans (with serial volumetric assessment). Interval scans may be 3, 6 or 12 months as determined by the nodule risk. Nodule risk is based on nodule type and size, and is used to guide subsequent actions / investigations (Table 1). A number of tools are available and are currently used within DHBs in New Zealand to identify which nodules need further investigation, helping to reduce the risk of harm from invasive investigations. In this study we will use the PanCan nodule risk management classification system to determine the malignancy risk of a nodule and determine recommended follow-up of the scan. The PanCan system has been used in international LCS studies including our Australian colleagues undertaking the International Lung Screening Trial (ILST). Table 1 below describes the nodule categories of risk for malignancy.

Table 1: PanCan nodule malignancy risk and associated actions for screening scan.

| **Category** | **PanCan nodule malignancy risk at screening scan** | **Action** |
| --- | --- | --- |
| 1 | No significant nodules: normal finding, nodule risk < 1.5% | No further action |
| 2 | Low risk: nodule risk 1.5% to < 6% | Repeat CT scan at 12 months (follow up scan)  No growth at 12m: repeat in further 12m and, if no growth then no further action*.  Any interval growth at 12 m: refer for diagnosis |
| 3 | Moderate risk: nodule risk 6% to < 30% | Repeat CT scan at 3m (follow up scan)  3m scan result: No growth: repeat scan at 12m intervals until no growth for 2 years and then no further action  If interval growth at 3m or any of the subsequent scans: refer for diagnosis  Consider referral for diagnosis if nodule risk 10 to < 30% |
| 4 | High risk: nodule risk $\geq$ 30% | Refer for diagnosis |
| 5 | Suspicious: mass/lesion; mediastinal or hilar lymphadenopathy irrespective of nodule size | Refer for diagnosis |

Cell-free DNA will be extracted from plasma following best practice guidelines^59^, before ctDNA analysis is undertaken using a DNA sequencing panel optimised to identify mutations in blood from primary and metastatic lung neoplasias using Ion ampliseq DNA sequencing technology. Based on variant allele frequency in the blood, DNA variants likely to originate from the patient’s germline will not be examined, by filtering out known common germline variants and/or variants present in blood at high frequency (>30%) consistent with germline origin. In this way, blood DNA variants likely to originate from the patient’s germline will be neither identified nor reported to the patient. The remaining DNA variants, which putatively originate from a neoplasia (ctDNA) will be curated against DNA variant databases which may identify their known occurrence in cancer and may also potentially suggest a likely tumour cell type of origin and may in some cases be ctDNA variants recognized as prognostic or predictive of therapeutic response. Some ctDNA variants identified, in particular those judged to have clinical actionability, may be confirmed using droplet digital PCR (ddPCR) technology in a clinically accredited test environment.

A range of non-genomic biomarkers may also be examined in blood serum, including CEA, CA125 and autoantibodies, using standard clinical procedures. Finally, the extent and impact of tobacco consumption will be estimated using one or more plasma DNA analysis methods, including: ddPCR assessment of the degree of hypo-methylation of CpG island cg05575921 in the promoter of the aryl hydrocarbon receptor repressor (*AHRR*) gene^60^. Correction will be made for patient-specific ratios of blood cell types using the complete blood count information. In up to six samples, the results of ddPCR-based *AHRR* gene hypo-methylation assessment will be confirmed using alternative analysis methods including IIlumina Infinium Methylation Beadchips^61^. As with ctDNA sequencing, germline DNA sequence data, which can be obtained from these Beadchips through deliberate analysis, will be neither obtained nor reported to the patient.

For individuals who have a lung nodule identified by CT scan (See Table 1, PanCan categories 2-5), ctDNA, protein biomarker analysis (if undertaken) and complete blood count will be analysed in an identifiable manner, to facilitate feedback of incidental findings if actionable ctDNA mutations were identified (see below). All remaining individuals, who have not had a lung nodule identified by CT scan, will have ctDNA, protein biomarker analysis (if undertaken) and complete blood count analysed after all patient samples are collected. These results will not be examined in an identifiable manner, rather, the blood biomarker and CT scan results for all individuals irrespective of whether they had a lung nodule identified by CT scan will anonymised before pooling for final analysis. Concordance between LDCT and biomarker results will be estimated and the marginal benefit of plasma biomarker data on the sensitivity of LDCT screening estimated using regression approaches, as we have undertaken previously^62^.

